## Abstract

**Background:**

Bacterial vaginosis is associated with increased transmission of sexually transmitted infections, preterm labor, post-surgical infections, and endometritis. Current treatment for symptomatic bacterial vaginosis includes antibiotics, such as metronidazole, which are 70–80 % effective at one month after treatment and result in high recurrence rates and secondary candida infections. Intravaginal boric acid has been used for over a hundred years to treat vaginal infections, such as bacterial vaginosis. Boric acid is inexpensive, accessible, and has shown to be an effective treatment for other infections, such as vaginal candidiasis. To date, there has been no clinical trial evaluation of boric acid effectiveness to treat bacterial vaginosis.

**Methods/Design:**

The BASIC (Boric Acid, Alternate Solution for Intravaginal Colonization) trial is a randomized, double-blinded, multicenter study. The study will enroll a minimum of 240 women of 16–50 years of age who are symptomatic with bacterial vaginosis. Eligible participants will have Amsel and Nugent scores confirming bacterial vaginosis. Women who are pregnant or menopausal or have other active co-infections will be excluded. Consenting participants who meet exclusion and inclusion criteria will be randomly assigned to one of three treatment groups: boric acid, metronidazole, or an inert placebo. Self-administration of treatment intravaginally for 10 days will be followed by clinical assessment at 7 and 30 days (days 17 and 40, respectively) after the end of the treatment phase. Primary outcome is a non-inferiority, per-protocol comparison of the effectiveness of boric acid with that of metronidazole at day 17, as measured by the Nugent score in 16–50 year olds. Secondary outcomes include: non-inferiority, intention-to-treat comparison of effectiveness of boric acid with that of metronidazole at day 17, analysis for both per-protocol and intention-to-treat at day 40, and safety considerations, including adverse effects requiring patient discontinuation of treatment.

**Discussion:**

This study will be the first to determine whether intravaginal boric acid is non-inferior to metronidazole in the treatment of bacterial vaginosis in symptomatic women.

**Trial registration:**

ClinicalTrials.gov NCT00799214, registered online Nov 10, 2008.

## Background

Bacterial vaginosis (BV) is thought to be more common than either vulvovaginal candidiasis or trichomoniasis, and to represent 40–50 % of all cases of vaginitis [1]. Bacterial vaginosis is associated with postpartum endometritis, increased risk of post-surgical infections, pelvic inflammatory disease, increased risk of spontaneous abortions, preterm rupture of membranes and delivery, and increased risk of sexually transmitted infection acquisition, including: human immunodeficiency virus, herpes simplex virus, *Neisseria gonorrhoeae*, *Chlamydia trachomatis*, and *Trichomonas vaginalis* [1–6]. Bacterial vaginosis is caused by a shift from the normal peroxidase-producing lactobacillus-dominant vaginal flora to a several-log increase in total bacterial colony count, which may include a mix of anaerobes, genital mycoplasmas, and *Gardnerella vaginalis* [1, 7]. Bacterial vaginosis is classically characterized by abnormal odor and vaginal discharge in symptomatic women, while 50 % of women with BV are asymptomatic [7, 8]. It can also be painful, and is associated with dysuria or dyspareunia in symptomatic women [8]. Bacterial vaginosis is diagnosed in the presence of three of the four Amsel criteria: elevated pH (>4.5); homogenous milky or creamy discharge; amine odor; and clue cells [4, 7, 9]. The gold standard for BV diagnosis is by Gram staining (Nugent score ≥7), demonstrating a decrease or absence of lactobacilli and the presence of other microbes that cause BV [4, 7, 9, 10].

Untreated women show a 30 % spontaneous resolution rate for BV [11, 12]. Current recommended antimicrobial treatments for BV in non-pregnant, symptomatic women include oral and intravaginal metronidazole or clindamycin [1, 8, 13]. Oral and intravaginal metronidazole are considered equivalent and effective treatments for BV [9, 11, 14–16].

Standard treatment with metronidazole, according to these trials, has imperfect cure rates (approximately 70–80 %) measured 1 month after treatment [9, 11, 12, 15–18] and high BV recurrence risks: 33 % at 3 months [19] and approximately 49–66 % at 1 year [18]. Metronidazole also carries a significant rate of side effects (10–20 % of women), especially with the oral metronidazole preparation [20], including secondary vaginal infection with candida [12, 14, 16]. At present, oral or vaginal metronidazole is the only recommended treatment option for recurrent BV, as is vaginal metronidazole for long-term suppression [9, 21].

Boric acid (H_3_BO_3_) has been used for over a hundred years for the treatment of vaginal infections and is commonly used by physicians and patients as an inexpensive, easy to use, accessible treatment of candidiasis and BV [22]. In addition to its proven effectiveness in the treatment of candidal infections, [22–31] including those that did not resolve with usual antifungal treatment [24–28], H_3_BO_3_ use seemed to be associated with a reduced number of co-infections with BV [25]. A retrospective study suggests clinical improvement in seven of nine patients following treatment with 600 mg intravaginal H_3_BO_3_ for 14 nights in women with a mixed infection of *T. glabrata* vaginitis and BV [25]. In an uncontrolled, non-randomized, retrospective chart review, when H_3_BO_3_ was added to nitroimidazole there was promising long-term (>88 % cure rate at 12 weeks after the study and 50 % at 36 weeks of follow-up) suppression of recurrent BV [32]. Based on the aforementioned study, the physician evidence reference resource ‘UpToDate*®*’ [21] recommends that intravaginal H_3_BO_3_ (600 mg for 21 days) be added to 7 days of metronidazole or tinidazole treatment to induce a remission prior to long-term suppression therapy. No studies to date have determined H_3_BO_3_ effectiveness in the treatment of acute, chronic, or recurrent BV.

The objective of this study was to determine whether intravaginal H_3_BO_3_ is comparable to standard treatment, metronidazole, for the cure of BV in symptomatic women.

### Research question

Among women 16–50 years old symptomatic with BV, is intravaginal treatment with H_3_BO_3_ non-inferior to metronidazole to achieve a Nugent score <7 (cure) by day 17?

### Null hypothesis

*H*_0_: proportion of women cured using H_3_BO_3_ ≤ metronidazole proportion of women cured using metronidazole − 10 %.

## Methods/Design

### Study design

Institutional review board approval was granted for this study through the University of British Columbia Clinical Research Ethics Board (H07-02330). Health Canada Clinical Trial Application Notice of Authorization was obtained on 10 May 2013 (company code 31784, file number 187476). This trial is registered with ClinicalTrials.gov (NCT00799214). This study conforms to CONSORT 2010 guidelines for randomized control trials.

Based on preliminary data, the success rate for the boric acid treatment group is predicted to be approximately 77–88 % [25, 32] in treating BV. Metronidazole would be expected to be 70–80 % [11, 12, 15–18] effective in treating BV, as compared with a 30 % success rate of a placebo group [11, 12]. The Nugent score is found to be >95 % sensitive [33] for detecting BV. We chose a non-inferiority limit of 10 %, as this will allow for a clinically relevant difference between the metronidazole treatment group and the boric acid group. Also, this is approximately 25 % of the expected difference between results obtained for the metronidazole standard treatment group and the placebo group. Accounting for a non-inferiority limit (delta) of 10 %, testing for a significance level of 0.05 and power of 80 %, we require approximately 63 subjects per group. To allow for a dropout rate of 25 %, we set a target rate of 80 subjects per treatment arm. If there is a true difference in favor of the experimental treatment of 8 %, then 126 patients (total for two groups of 63) are needed, to be 80 % sure of the upper limit of a one-sided 95 % confidence interval, using a binary outcome, non-inferiority trial power calculator [34].

We felt it important to include a placebo treatment arm in this study for different reasons: (1) this is the first randomized controlled trial to use intravaginal H_3_BO_3_; thus, comparing it to placebo for safety and effectiveness would be of clinical interest (that is, perhaps it is not comparable to metronidazole in effectiveness but it is still significantly better than placebo), (2) having a placebo group in a non-inferiority trial acts as a sensitivity assay and internal validator for this type of trial [35], (3) comparing metronidazole effectiveness and safety with results obtained for a placebo group in 16–19-year-olds has not previously been done and would also be of clinical interest.

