### Participants and eligibility

Women who present to their clinician at participating family practice clinics with symptoms of BV are offered an opportunity to participate in the study. Participants are given the informed consent form explaining the three possible treatment arms, and that participation will include three visits (the initial visit, day 0; day 17–19 [7–9 days after the treatment end to measure the primary endpoint]; and day 40–42 [30–32 days after the treatment end as a secondary endpoint]) involving three examinations, including a pregnancy test. There are no visits to the clinic while the participants are administering the 10-day treatment unless there are any concerns. Women are included in the study if they are symptomatic for BV, meet three of four Amsel criteria on the initial day of the study and subsequently have a swab graded with a Nugent score ≥7. Detailed eligibility criteria are listed in Table 1. In general, participants cannot be pregnant, menopausal, have another vaginal infection, or have an intrauterine device. Written consent is obtained prior to treatment intervention. Women who choose to participate receive their medication for free. There is a draw for recruited women to win a small gift certificate.

**Table 1 Tab1:** Eligibility criteria

Inclusion criteria	Exclusion criteria
Must be 16–50 years old and pre-menopausal. Capable of giving written informed consent.	Younger than 16 or post-menopausal.
Fluent spoken and written English.	Menstruating at diagnosis.
Agrees to examination on enrollment day, day 17–19 and day 40–42.	Symptoms so severe as to make allocation to placebo unacceptable to the woman.
Has a negative pregnancy test during the study. Agrees to follow study protocol and is reliable for follow-up.	Currently pregnant or at high risk for pregnancy.
Has documented bacterial vaginosis infection by positive vaginal swab (minimum Nugent score of ≥7) and meets three of four Amsel criteria.	Current active sexually transmitted infection (chlamydia, gonorrhea, trichomonas).
Agrees to refrain from vaginal intercourse for the 10 days of treatment (or to use non-lubricated non-latex condoms if unavoidable). Agrees not to douche or use any intravaginal products during treatment (including tampons, medications, devices).	Current yeast infection as determined by history, physical examination, and swab analysis.

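### 80 per arm leaves 60 evaluable after 25% dropout, not the required 63, and the 63 gives 80% power only if boric acid is 8 points better; at equality power is about 36%

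*Protocol article*

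**What the plan says.** All the sample size figures are in the protocol article, Study design. For a 10-point margin the text reads "testing for a significance level of 0.05 and power of 80 %, we require approximately 63 subjects per group". For 25% dropout it then says "we set a target rate of 80 subjects per treatment arm". Later in the same paragraph it says that 126 women in two groups suffice if the experimental treatment is truly 8 points better, with a one-sided 95% limit. Metronidazole is expected to cure 70-80%; no single planning rate is given for either arm.

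On the boric acid rate, the section says "the success rate for the boric acid treatment group is predicted to be approximately" 77-88%, citing two references. The Background describes both. In one, a retrospective chart review, boric acid "was added to nitroimidazole there was promising long-term" suppression, with more than 88% cured at 12 weeks. The other, also retrospective, reports "clinical improvement in seven of nine patients" with mixed yeast and bacterial vaginosis infection.

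Statistical considerations makes the primary analysis a per-protocol comparison of Nugent-defined cure at day 17, and treats missing data as covered by the 25% allowance.

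**The concern.** Three stated figures do not carry the meaning given to them. The enrolled number, after the stated loss, falls below the stated requirement. The sentence giving 63 names the margin, the significance level and the power, but not the treatment advantage without which 63 is far too few. And the rate predicted for boric acid alone rests partly on women who also received a nitroimidazole.

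A reader who takes the 80% at face value would think the trial well placed to show non-inferiority if the two treatments work equally well. It is not. A confidence interval crossing the margin could then be read as evidence against boric acid when the trial was simply too small to settle the question.

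**Working it through.** **Inputs.** From Study design: margin 0.10, one-sided 0.05, power 80%, true advantage 0.08, metronidazole 70-80%, dropout 25%, 63 per group, 80 per arm. Assumption: metronidazole 75% (the midpoint), hence boric acid 83%. Results are also shown at 70% and 80%.

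**1. Reproduce 63.** With the unpooled normal approximation,

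n = (z₀.₉₅ + z₀.₈₀)² × [p_M(1 − p_M) + p_B(1 − p_B)] / (0.10 + p_B − p_M)²

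- 75% v 83%: (1.645 + 0.842)² × (0.1875 + 0.1411) / 0.18² = 62.7, so 63. The protocol's figure reproduces.
- 70% v 78%: 73.
- 80% v 88%: 51.
- One-sided 0.025 at 75% v 83% would give 80 evaluable per group, so 63 implies one-sided 0.05.

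**2. Dropout.**

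- 80 × (1 − 0.25) = 60, which is 3 short of 63.
- Correct inflation: 63 / 0.75 = 84 per arm, or 3 × 84 = 252 against 240.
- Multiplying instead of dividing: 63 × 1.25 = 78.75, or 79, which rounds up to 80.
- 80 per arm yields 63 only if the loss is at most 1 − 63/80 = 21.25%.

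**3. Power with the 8-point advantage.** Power = Φ[(0.10 + p_B − p_M)/SE − 1.645], where SE = √{[p_M(1 − p_M) + p_B(1 − p_B)]/n}.

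| Metronidazole v boric acid | n = 63 | n = 60 |
|---|---|---|
| 70% v 78% | 74.8% | 73.0% |
| 75% v 83% | 80.2% | 78.4% |
| 80% v 88% | 87.0% | 85.6% |

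**4. Power at true equality.** The same formula with p_B = p_M:

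| Cure rate in both arms | n = 63 | n = 60 |
|---|---|---|
| 70% | 33.7% | 32.6% |
| 75% | 36.4% | 35.2% |
| 80% | 40.4% | 39.1% |

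For scale, 80% power at equality needs 232 evaluable per arm at 75% (198 at 80%, 260 at 70%).

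**5. The predicted boric acid rate.** 7/9 = 77.8%, the lower end, with an exact 95% confidence interval of 40-97%. It is clinical improvement in a mixed infection. The upper end, 88%, is combination treatment assessed at 12 weeks. Neither is boric acid alone by Nugent score at day 17.

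**The case against.** Much can be said for the protocol. The requirement is worded as approximately 63 and the 80 as a minimum, and losing three women per arm lowers power by under 2 points. If metronidazole cures 80%, 60 evaluable still gives about 86%. The 8-point assumption is disclosed in the same paragraph, and the Background is candid about the weakness of both sources. These points stand, and they keep the dropout slip small. They do not make 80 × 0.75 reach 63, supply the missing planning rates, or make a combination-treatment result a boric acid rate.

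Three stronger readings are tempting but not supported:

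- A reader might infer that the power calculation does not address the non-inferiority question. It does. The null hypothesis keeps the 10-point margin; what is optimistic is the alternative under which power was computed.
- A reader might infer that the 8 points were taken from the two cited sources. The midpoints of the two ranges, 82.5% and 75%, differ by 7.5, which is suggestive, but the protocol never says how the 8 was derived.
- A reader might subtract further women because packs are given out on day 0 and participants "subsequently have a swab graded with a Nugent score ≥7". The documents give no rate for such removals. Since Participants and eligibility, with Table 1, makes a Nugent score of at least 7 a condition of inclusion, the target can be read as counting confirmed women only.

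The power figures here use the one-sided 0.05 of the sample size calculation. Statistical considerations also sets a 0.01 threshold across four analyses; where that applies, power is lower.

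**Conclusion.** The point holds as three errors of statement. The 80 per arm falls short of the protocol's own requirement: 60 rather than 63 evaluable, with about 78% power instead of 80% at 75% v 83%. That part alone is minor. The claim that 63 per group gives 80% power for a 10-point margin holds only with the 8-point advantage; at equality power is about 36% with 63 (34-40%) and about 35% with 60 (33-39%). This matters most for reading an inconclusive result. And the range called the boric acid success rate does not describe boric acid alone on the trial's endpoint.

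The 63, 60 and 84 need no outside assumption. The central power figures rest on 75% for metronidazole, which the protocol does not state but which reproduces its 63; the ranges cover its stated 70-80%.

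**What to change.** Revise the sample size paragraph in Study design, with no change to enrolment:

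- Keep 80 per arm, but say that 25% dropout leaves 60 evaluable, with about 78% power at one-sided 0.05, and that 63 evaluable would need 84 per arm.
- State the assumed cure rates, 75% v 83%, and say in the sentence giving 63 that 80% power depends on a true 8-point advantage.
- Add power at equality: about 35% with 60 evaluable (33-39% for cure rates of 70-80%), or 36% with 63 (34-40%).
- Stop presenting the combination-therapy 88% as the predicted rate for boric acid alone, and describe the 77% as clinical improvement in seven of nine women with mixed infection.

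The cost is a few sentences and a less favourable stated power.

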### Study setting

Recruitment began February 2014 for a minimum of 240 volunteers through participating family practice clinics in British Columbia, Canada. Volunteer participating clinics represent a spectrum of different types of practice across British Columbia: rural, remote, urban, First Nations and non-First Nations communities, single and multi-clinician practices, general family practice offices, women’s health clinics, and youth clinics. Clinics were recruited to the study through province-wide medical journal advertisements, university family practice departmental email advertisements, personal emails, faxes, phone calls and in person. Eligible clinics agreed to recruit five or more participants meeting inclusion and exclusion criteria and to use the study treatments and prepared packages provided.

### Participants and eligibility

Women who present to their clinician at participating family practice clinics with symptoms of BV are offered an opportunity to participate in the study. Participants are given the informed consent form explaining the three possible treatment arms, and that participation will include three visits (the initial visit, day 0; day 17–19 [7–9 days after the treatment end to measure the primary endpoint]; and day 40–42 [30–32 days after the treatment end as a secondary endpoint]) involving three examinations, including a pregnancy test. There are no visits to the clinic while the participants are administering the 10-day treatment unless there are any concerns. Women are included in the study if they are symptomatic for BV, meet three of four Amsel criteria on the initial day of the study and subsequently have a swab graded with a Nugent score ≥7. Detailed eligibility criteria are listed in Table 1. In general, participants cannot be pregnant, menopausal, have another vaginal infection, or have an intrauterine device. Written consent is obtained prior to treatment intervention. Women who choose to participate receive their medication for free. There is a draw for recruited women to win a small gift certificate.

**Table 1 Tab1:** Eligibility criteria

Inclusion criteria	Exclusion criteria
Must be 16–50 years old and pre-menopausal. Capable of giving written informed consent.	Younger than 16 or post-menopausal.
Fluent spoken and written English.	Menstruating at diagnosis.
Agrees to examination on enrollment day, day 17–19 and day 40–42.	Symptoms so severe as to make allocation to placebo unacceptable to the woman.
Has a negative pregnancy test during the study. Agrees to follow study protocol and is reliable for follow-up.	Currently pregnant or at high risk for pregnancy.
Has documented bacterial vaginosis infection by positive vaginal swab (minimum Nugent score of ≥7) and meets three of four Amsel criteria.	Current active sexually transmitted infection (chlamydia, gonorrhea, trichomonas).
Agrees to refrain from vaginal intercourse for the 10 days of treatment (or to use non-lubricated non-latex condoms if unavoidable). Agrees not to douche or use any intravaginal products during treatment (including tampons, medications, devices).	Current yeast infection as determined by history, physical examination, and swab analysis.
Agrees to abstain from alcohol during the 10 days of treatment (from 24 hours before through 72 hours after taking study medication).	History of pelvic inflammatory disease. Allergy to metronidazole.
Agrees to no new medications or antibiotics during treatment.	Currently breast feeding.
Has no currently active sexually transmitted infection as determined by history, physical examination, and swab analysis negative for chlamydia, gonorrhea, candidiasis, or trichomonas.	Any open wound, excoriation, or vaginal irritation, including Bartholin’s cyst, abscess, and herpes simplex viral lesion, as determined by physical exam.
	Presence of another vulvar, vaginal or medical condition, including cervical neoplasia or treatment, or medical device, including intrauterine device, that might confound treatment response.
	Using lithium, anticoagulants or disulfiram drugs.
	Any antifungal or antibiotic use 14 days prior to enrolment.
	Papanicolaou smear taken within one week of enrolment.
	Meeting three of four Amsel criteria but having a Nugent score <7.

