### Intervention and control groups

On day 0, the enrolled participants will be blindly and randomly assigned to one of three 10-day treatments (minimum of 80 women per treatment arm): (1) placebo (emollient cream); (2) H_3_BO_3_ (600 mg H_3_BO_3_ compounded in emollient cream); (3) metronidazole (10 %, for a total of 37.5 mg metronidazole) intravaginal cream (Sanofi-Aventis Canada Inc. Product DIN 01926861) packaged by the study pharmacist. There is no detectable difference between the treatments in either appearance or scent.

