### Safety assessments

Emergency telephone contact with the investigators will be available for any questions or problems related to the treatment. On day 5 of the treatment, the participant will receive a call, text, or email from one of the investigators to determine and record compliance, side effects, BV symptoms, and satisfaction with treatment. The study pharmacist will be informed by the recruiting clinician of the participant’s full name, date of birth, and personal health number, and the study number assigned, so that the study pharmacist can enter the medication name into the British Columbia PharmaNet Database (the provincial pharmacy database). This safety measure ensures that subsequent treating physicians throughout the province will have access to details of the treatment received, in case of a safety concern and a need to unblind the participant’s medication should the participant present with an emergency. Non-emergency access to the provincial pharmacy database is not allowed, to protect the participant’s identification of the blinded treatment.

If at any time the participant reports intolerable side effects (vaginal discomfort, intolerable vaginal discharge, urticaria, or secondary yeast infection) during treatment, or exacerbation of symptoms at any point, she may voluntarily discontinue the treatment and leave the study without prejudice, and her doctor or another physician may provide treatment as per usual standard of care.

As neither metronidazole nor H_3_BO_3_ treatments provided to patients are in amounts considered toxic when taken intravaginally or if accidentally ingested, should there be any occurrence of serious adverse effects (neurological, cardiac, respiratory, gastrointestinal, or anaphylactic reactions) during any of the treatments, the study will be put on hold until an investigation can be held. In the case of serious adverse effects found to be caused by the treatment, the study will be stopped, and the study unblinded and decoded by the study pharmacist. The investigators, participants, and clinicians involved in the study would be informed for the reason for stopping the study.

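### Table 1 excludes known allergy to metronidazole only, although the blinded packs also contain boric acid and an emollient cream

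*Protocol article*

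**What the plan says.** The section on participants and eligibility presents Table 1 as the full list: "Detailed eligibility criteria are listed in Table 1". The table has one allergy entry, "Allergy to metronidazole", which shares a cell with an unrelated criterion: "History of pelvic inflammatory disease. Allergy to metronidazole". No line names boric acid, the emollient cream or excipients.

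The section on intervention and control groups describes the other two products as "1) placebo (emollient cream); (2) H_3_BO_3_ (600 mg H_3_BO_3_ compounded in emollient cream"; the third is a metronidazole cream whose base is not described. The packs are stated to be indistinguishable, and the target is a "minimum of 80 women per treatment arm".

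The safety assessments section has two levels. Intolerable effects such as vaginal discomfort or urticaria allow the woman to stop and leave. A hold on the study applies "should there be any occurrence of serious adverse effects (neurological, cardiac, respiratory, gastrointestinal, or anaphylactic reactions) during any of the treatments", and the study stops only if the serious effect is found to be caused by treatment. Under outcomes and assessment, stopping for side effects, or complaining of intolerable ones, counts as failure on the secondary safety outcome.

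**The concern.** An allergy criterion in a blinded trial should match what the packs contain, because once a woman is enrolled nobody at the clinic can steer her away from a particular product. Here it covers one of the three products.

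The Background says that boric acid "is commonly used by physicians and patients as an inexpensive, easy to use, accessible treatment of candidiasis and BV". Earlier exposure among candidates is therefore plausible, and with it the possibility that some know of an earlier reaction. Treatment is self-administered at bedtime, no clinic visit is planned during the 10 days, and the scheduled contact in that time is one call, text or email on day 5.

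Two things are at stake. The first is protection of a woman with a known reaction. The second is even-handedness in the tolerability comparison of the two active drugs, in a trial that describes itself as the first randomised one of intravaginal boric acid and gives safety as a reason for its placebo arm.

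**Working it through.** The plan states no figure on this point, so the check is mainly textual. The arithmetic in step 5 is illustration only.

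**1. Pack contents against the allergy exclusion**

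- Metronidazole (metronidazole arm): known allergy excluded.
- Boric acid (boric acid arm): not named.
- Emollient cream (placebo and boric acid arms): not named.
- Base of the metronidazole cream: not described, so nothing can be concluded about it.

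**2. Do other lines of Table 1 close the gap?**

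- The line on wounds, excoriation and vaginal irritation is judged by physical examination on the day. A past reaction that has resolved would not be found.
- The line that begins "Presence of another vulvar, vaginal or medical condition, including cervical neoplasia or treatment" is limited to what might confound treatment response. A clinician could stretch it to hypersensitivity, but it does not say so. Naming metronidazole allergy separately suggests that the authors did not rely on it for allergy.

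**3. Direction of any bias**

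Let *b* be the proportion of enrolled women with a known reaction to boric acid and *e* the proportion with a known reaction to the emollient. Suppose that all of them fail on tolerability when exposed, which is an upper bound, and that the two groups do not overlap. Known metronidazole reactors contribute nothing, because they are excluded.

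- Extra failures in the boric acid arm: up to *b* + *e*.
- Extra failures in the placebo arm: up to *e*.
- Boric acid minus placebo: (*b* + *e*) − *e* = *b*. Reactions to the base cancel.
- Boric acid minus metronidazole: between *b* and *b* + *e*, depending on how far the undescribed metronidazole base provokes the same reactions.

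The sign is against boric acid. The documents give neither *b* nor *e*.

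**4. Consequence for the trial**

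- Discomfort, urticaria and similar effects: that woman may leave, and the trial continues.
- Serious effect, including an anaphylactic reaction: hold and investigation.
- Serious effect found to be caused by treatment: stop and unblind.

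These rules apply to every arm alike.

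**5. Illustration of size**

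Let *f* be an assumed proportion of enrolled women with a known reaction to a component of the pack. Expected number per arm = 80 × *f*. Chance of at least one among *n* women = 1 − (1 − *f*)^*n*. Here *n* = 80 for a reaction to boric acid (one arm) and *n* = 160 for a reaction to the emollient (two arms).

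| Assumed *f* | Expected per arm of 80 | At least one in 80 | At least one in 160 |
|---|---|---|---|
| 0.25% | 0.2 | 18% | 33% |
| 0.5% | 0.4 | 33% | 55% |
| 1% | 0.8 | 55% | 80% |
| 2% | 1.6 | 80% | 96% |

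Even if every such woman stopped, the discontinuation proportion in an affected arm would rise by *f* itself, that is by 0.25 to 2 percentage points.

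If a share *s* of these reactions were serious, the chance of at least one serious reaction among 160 is 1 − (1 − *f* × *s*)^160. With *f* = 0.5% and *s* = 1% this is 1 − (1 − 0.00005)^160 = 0.8%. With *f* = 2% and *s* = 10% it is 1 − (1 − 0.002)^160 = 27%. So wide a range on assumed inputs shows that the documents cannot settle the figure.

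**The case against.** Several safeguards already stand between a known reactor and a pack. The consent form explains the three possible treatments, so a woman who knows that she reacts to boric acid learns that she might receive it. The clinician takes a history on day 0 and confirms eligibility on study forms that are not shown and might carry a broader allergy question. There is emergency telephone access, and withdrawal is free. The Background reports no reaction to boric acid, and common use does not show that any candidate has a known one.

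Much of this stands, and it lowers the likely number of women affected. It does not mend the criterion. Explaining the arms is not said to include the cream base, and the history is not said to include allergy to the other components. Nor is this a detail lost by condensing a protocol: the article prints what it calls the detailed list and states an allergy rule, and that rule is too narrow for the packs that it describes.

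Three stronger readings are tempting, and the documents do not support them.

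- A reader might infer that any one reaction in a known reactor could end the trial. Ordinary reactions lead only to that woman leaving. A hold needs a serious effect, and a stop needs that effect to be attributed to treatment.
- A reader might infer a measurable tilt in the safety results. The direction follows from the text, but the size does not, because no hypersensitivity rate is given for boric acid or the emollient. Reactions to the base do not bias boric acid against placebo.
- A reader might infer harm to the non-inferiority result. The sample size, the 10% margin and the Nugent-based rule do not depend on this criterion.

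**Conclusion.** The point holds in limited form. The allergy exclusion in Table 1 does not match the pack contents, so a woman with a known reaction to boric acid or the emollient is eligible as the plan is written. This is an avoidable participant risk. Any resulting bias in the secondary tolerability comparison of boric acid with metronidazole would run against boric acid.

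The size is unknown and probably small: fewer than two women expected per arm of 80 at assumed rates up to 2%, and that as an upper bound in which every such woman consents, is enrolled and stops treatment. The link to stopping the trial exists only through a serious reaction attributed to treatment. The primary analysis is not affected. The conclusion rests on Table 1 being the complete list, as the article presents it.

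**What to change.** Reconcile the allergy exclusion in Table 1 with the section on intervention and control groups, so that it covers known allergy or hypersensitivity to any component of the study packs: metronidazole, boric acid, and the emollient or other cream base. Put the question in the day-0 history, which is already taken, and on the eligibility form.

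The cost is more than a change of wording. Recruitment is open at many clinics under an ethics approval and a Health Canada authorisation, so a minor amendment to the protocol and the form is needed, and sites must be told. The number of extra exclusions should be negligible, and the sample size and analysis need no change. If the unshown eligibility form already asks about all components, it is enough to bring Table 1 into line with it.
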